### Data management

A member of the local trial team will submit the data into the trial database. Access to the eCRF system will only be provided to staff with relevant authority delegated to them on the site’s delegation log. At enrolment, participants will be given a unique subject number and data will be entered under this subject number onto the trial database. No personal identifiable data will be stored on the trial database. Any personal identifiable data will be stored on a dedicated secure trial area, part of University College London’s (UCL) Data Safe Haven.

The trial is compliant with the requirements of General Data Protection Regulation (2016/679) and the Data Protection Act (2018). All investigators and trial site staff will comply with the requirements of the General Data Protection Regulation (2016/679) with regard to the collection, storage, processing and disclosure of personal information, and will uphold the Act’s core principles.

### Statistical methods

#### Validating image protocol

Patients will be assessed with both imaging procedures (fhSPECT and SPECT/CT), with SPECT/CT being considered the gold standard—to allow assessment of sensitivity and specificity of fhSPECT (including positive predictive value and negative predictive value). The agreement between fhSPECT and SPECT/CT will be recorded as either agree or disagree and will be calculated with an exact 95% CI. Two independent assessors will consider each pair of scans. We will investigate the agreement between these assessors and quantify the corresponding intra-class correlation.

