**Methods and analysis:**

The design is a prospective multicentre cohort trial to understand the lymphatic drainage pattern in 150 patients with OPC and unilateral neck metastases. The trial has two phases: (1) *imaging phase (n=75)*—aim: develop an imaging protocol to establish the lymphatic drainage pattern in a population of patients with proven unilateral neck metastasis from OPC. The intervention will involve peritumoural injection of radiotracer followed by fhSPECT scan under general anaesthesia (GA) (at time of examination under anaesthetic). A SPECT/CT scan (gold standard for lymphatic mapping) will be carried out subsequently as a comparator. The primary outcome is the rate of contralateral drainage. Secondary outcome is the accuracy of fhSPECT versus SPECT/CT. The number of contralateral nodes on SPECT/CT will be used as the denominator in calculating the sensitivity of fhSPECT in independently verified images. fhSPECT should achieve sensitivity >94%. A minimum number of 20/75 patients will be required to demonstrate contralateral drainage to proceed to the surgical stage. An imaging substudy (n=20) aims to develop a secondary imaging protocol in the event of <94% sensitivity of intraoperative fhSPECT. To investigate the sensitivity of outpatient imaging (single injection of radiotracer and SPECT/CT) compared with gold standard (SPECT/CT from initial imaging phase) and the acceptability of outpatient injection compared with under GA. Twenty patients from the imaging phase with easily accessible tumours will be invited to undergo a second imaging; (2) *Surgical phase (n=75)*—aim: demonstrate the utility of surgically staging the contralateral neck using sentinel node biopsy (SNB). The primary outcome of this surgical phase is the occult metastatic rate of contralateral nodes (positive SNB). The contralateral drainage rate will be identified during the imaging phase, with an expected SNB positive rate of excised nodes ranging from 25% to 40%.

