### Imaging phase

Four submucosal peritumoural injections of radiotracer are administered under direct/endoscopic vision during EUA.After 15 min drainage, fhSPECT scan is undertaken (declispeSPECT, Surgiceye). Separate scans of both the contralateral and ipsilateral neck are taken.Following recovery (and up to 24 hours later), conventional SPECT/CT is undertaken (gold standard imaging).

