#### Surgical phase

The surgical phase is planned to follow immediately from the imaging phase if specified outcomes are met. The precise surgical protocol is to be informed by outcomes of the prior imaging phase. Either:

Intraoperative peritumoural tracer injection and fhSPECT imaging of contralateral sentinel node in theatre under a single GA.

or

Single intratumoural injection in the outpatient setting, followed by conventional SPECT/CT.

Either of the above is followed by an SNB (as per standard protocol)^23^ of contralateral nodes during EUA. As per accepted evidence, the presence of viable individual tumour cells or greater is considered metastatic nodes.^24^ The result of the SNB will be discussed with the patient and the oncology team prior to further treatment, but the recommendation will be based on the decision of the multidisciplinary team (MDT). This trial is not powered to recommend changes in treatment based on the SNB result.

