#### Imaging phase outcome measure data collection

Each assessor fulfils a CRF per case with three questions:

Are there contralateral nodes on SPECT/CT? No/Yes (record neck level).Are there contralateral nodes on fhSPECT? No/Yes (record neck level).Do the contralateral nodes co-localise? Yes/No.

If contralateral nodes are shown in SPECT/CT but not on fhSPECT, this will be recorded as a false negative result (unless these can be attributed to second echelon nodes) for fhSPECT and vice versa. Contralateral drainage on either modality will be recorded as a true positive result. fhSPECT should achieve sensitivity >94% compared with SPECT/CT.

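### fhSPECT misses, but not hits, can be set aside as second echelon after the fact, which can only favour fhSPECT against the 94% sensitivity target

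*Protocol article*

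**What the plan says.** All places are in the protocol article.

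- **Reading.** Statistical methods, Validating image protocol: "Two independent assessors will consider each pair of scans".
- **Form.** Imaging phase outcome measure data collection: "Each assessor fulfils a CRF per case with three questions". The questions are, in order, contralateral nodes on SPECT/CT, contralateral nodes on fhSPECT, and co-localisation. None asks about echelon.
- **Miss rule.** Same section, where SPECT/CT shows a contralateral node that the earlier scan fails to show: "this will be recorded as a false negative result (unless these can be attributed to second echelon nodes) for fhSPECT and vice versa". No criterion for the attribution is printed. Drainage seen on either modality is a true positive.
- **Denominator.** Outcomes, Imaging phase: sensitivity is taken over the contralateral nodes on SPECT/CT. No second-echelon exclusion appears there.
- **Timing.** Planned interventions, Imaging phase: fhSPECT follows 15 minutes of drainage. SPECT/CT follows recovery, up to 24 hours later.
- **Target and use.** "fhSPECT should achieve sensitivity >94% compared with SPECT/CT". The Abstract says the substudy "aims to develop a secondary imaging protocol in the event of <94% sensitivity of intraoperative fhSPECT". Under Surgical phase, "The precise surgical protocol is to be informed by outcomes of the prior imaging phase", with intraoperative fhSPECT or outpatient injection with SPECT/CT as the two routes.
- **Condition for proceeding.** Outcomes: at least 20 of 75 patients must show contralateral drainage.

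**The concern.** The exception is asymmetric. Whether a node is second echelon becomes a question only when the two scans disagree in the direction that hurts fhSPECT. If fhSPECT saw a second-echelon node, nothing removes it from the hits. The discretion therefore works one way on sensitivity, and it is exercised by someone who already knows there was a miss. The gap between 15 minutes and up to 24 hours makes onward drainage a plausible explanation for many late nodes, so the exception is easy to invoke.

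The two sections also give different sensitivities from the same data, depending on whether an excused node stays in the denominator.

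A second, weaker point concerns the reading itself. The assessors are independent of each other, but the unit they consider is the pair, and the single form records the reference scan before the index scan. Nothing printed keeps the fhSPECT read free of the SPECT/CT result. If a faint fhSPECT focus is called because SPECT/CT pointed to it, that too pushes sensitivity up.

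At stake is the figure that informs whether intraoperative fhSPECT or the outpatient SPECT/CT route guides contralateral biopsy in the surgical phase.

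**Working it through.** **1. The plan's own figures.** Sample size, Imaging phase gives n = 75, expected agreement 96%, null 88%, one-sided 5%, 80% power and an exact 95% CI about 10% wide. Exact binomial, rejecting at 71 or more agreements of 75: type I error 0.0449, power 0.819. Clopper-Pearson for 72/75 is 88.8% to 99.2%, width 10.4%. The figures reproduce. They concern overall agreement in 75 patients, not sensitivity among contralateral-positive findings, so they do not cover the 94% target.

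**2. Size of the denominator (assumption).** Let D be the number of SPECT/CT-positive contralateral findings. The article does not give D. Sample size, Surgical phase expects 15 to 23 of 75 patients with contralateral sentinel nodes. Proceeding needs 20 of 75, but that counts drainage on either modality. A patient may have more than one node. I take D from 15 to 30.

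**3. Misses allowed.** With k misses, sensitivity = (D − k)/D. Exceeding 94% allows no miss for D up to 16, one for D = 17 to 33, and two for D = 34 to 50.

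**4. Effect of one excused miss,** if the node leaves the denominator: (D − k)/(D − 1).

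| D | k | No excuse | One miss excused | Crosses 94%? |
|---|---|---|---|---|
| 15 | 1 | 14/15 = 93.3% | 14/14 = 100% | yes |
| 17 | 2 | 15/17 = 88.2% | 15/16 = 93.75% | no |
| 20 | 2 | 18/20 = 90.0% | 18/19 = 94.7% | yes |
| 23 | 2 | 21/23 = 91.3% | 21/22 = 95.5% | yes |
| 30 | 2 | 28/30 = 93.3% | 28/29 = 96.6% | yes |

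For D from 12 to 40, the smallest failing number of misses becomes a pass at every value except 17 and 34.

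**5. The two sections side by side,** D = 20, two misses, one excused:
- detected nodes over all SPECT/CT nodes: 18/20 = 90.0%;
- excused node dropped: 18/19 = 94.7%;
- excused node kept in the denominator but not counted as a false negative: 1 − 1/20 = 95.0%.

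The reading chosen decides the result. A faint node called on fhSPECT because SPECT/CT showed it would also give 19/20 = 95.0%.

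**6. What symmetry changes (illustration).** Suppose that, of the same 20 nodes, one missed and three detected are second echelon. Excluding only the miss gives 18/19 = 94.7%. Excluding all four gives 15/16 = 93.75%.

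**7. Chance of exceeding 94%,** D = 20, findings independent, true sensitivity s, K misses. Without an excuse this is P(K ≤ 1). If one miss is always excused it is P(K ≤ 2), with P(K = k) = C(20,k)(1 − s)^k s^(20 − k).

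| s | No excuse | One miss excused |
|---|---|---|
| 85% | 17.6% | 40.5% |
| 90% | 39.2% | 67.7% |
| 94% | 66.0% | 88.5% |

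This shows what a single excuse can do. It does not forecast how often the exception will be used.

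**The case against.** **The exception has a sound rationale.** The aim is to map sentinel nodes. Onward drainage that appears only on a scan hours later is not a failure of a scan at 15 minutes, and removing such nodes corrects the target. This stands. What remains is that the rule is triggered only by misses.

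**Blinding may be specified elsewhere.** A reader might infer that fhSPECT is read with the SPECT/CT result known. The article does not say so. The order of questions on a form is not a reading order, co-localisation needs both scans in any design, and a locked fhSPECT read is neither stated nor ruled out. The article condenses a fuller protocol that may settle it. This stands, so the reading order is only a supporting point. The miss rule is printed and does not depend on it.

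**The sections may not conflict.** The data collection rule can be read as qualifying the denominator under Outcomes. That is possible, but the article does not say whether an excused node leaves the denominator, and step 5 shows that it matters.

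**Sensitivity above 94% is not the formal go/no-go.** Correct. That condition is 20 of 75 with contralateral drainage, and the surgical protocol is only said to be informed by the imaging results. The Abstract nevertheless ties the alternative imaging protocol to sensitivity below 94%.

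**The example is chosen.** D is assumed, the denominator is nodes rather than patients, and one excuse does not always change the result. All true; hence the range in step 4.

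**Conclusion.** The point holds for the miss rule as printed. Applied only to misses, the second-echelon exception can raise fhSPECT sensitivity and cannot lower it, and it is not reflected in the denominator under Outcomes. With an assumed 15 to 30 SPECT/CT-positive findings, the target tolerates no miss or one, so a single excused miss usually moves the result across 94% (18/20 = 90.0% to 18/19 = 94.7%), though not at every denominator: if the node is dropped, not at 17. The actual bias cannot be computed from the article, because neither the node count nor the frequency of second-echelon nodes is given.

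Three stronger readings are not supported: that unblinded reading is established, that 94% is the formal condition for starting surgery, and that one excused miss always reverses the result. The matter should be corrected before the imaging-phase sensitivity is used to inform the surgical imaging route. It does not undermine the primary outcome of that phase.

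**What to change.** 1. Have the same two assessors record and lock the fhSPECT read before SPECT/CT is shown.
2. At a separate SPECT/CT read, without knowledge of fhSPECT, label each contralateral node first or second echelon by a criterion written in advance. The documents do not show that SPECT/CT alone can always separate the two, so a node that cannot be labelled should stay in the denominator.
3. Exclude second-echelon nodes from numerator and denominator whether or not fhSPECT saw them.
4. Score co-localisation last.
5. Report sensitivity over all SPECT/CT contralateral nodes alongside.
6. Align the denominator under Outcomes with the miss rule under Imaging phase outcome measure data collection.

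Cost: a revised form, an added echelon item and a second short reading session, with no extra readers or patients. Recruitment began in July 2022, so cases already assessed would need their stored images re-read. Assessors may remember some of them, and the report should say which cases were re-read.

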#### Surgical phase

We will quantify the proportion of SNB patients with sentinel nodes on the opposite side of the neck with an exact 95% CI.

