## Abstract

**Introduction:**

Treatment of the node negative contralateral neck in oropharyngeal cancer (OPC) remains debated, with no clear consensus. Prophylactic contralateral neck treatment (either surgically or via irradiation) is generally recommended when the estimated risk of occult nodal metastasis is >20%. Unfortunately, patients undergoing bilateral neck treatment often require long-term supportive care for swallowing dysfunction. Reducing the impact of treatment on long-term quality of life is key in patients with OPC who have a good prognosis and tend to be young and fit at presentation. Lymphatic mapping and the use of free-hand single photon emission CT (fhSPECT) combined with sentinel lymph node biopsy is a novel approach to address this clinical need. The Lymphatic mapping Of Oropharyngeal Cancer trial aims to (a) validate a lymphatic mapping protocol in OPC using new technology (fhSPECT) with radiotracers and (b) establish lymphatic drainage patterns and the occult metastatic rate in the contralateral neck in OPC.

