#### Surgical phase

Occult metastatic rate of contralateral nodes (positive SNB).

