### Surgical phase

75 patients will be considered for SNB. Of these, 20%–30% (15–23 patients) are expected to have sentinel nodes on the opposite side of the neck. An exact 95% CI for this proportion is expected to have precision of ±11%.

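### The surgical phase names positive sentinel node biopsy as its primary outcome, but its stated precision (±11%) and its only stated analysis are for contralateral drainage

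*Protocol article*

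**What the plan says.** Four places in the protocol article bear on the surgical phase.

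- **Abstract, Methods and analysis.** "The primary outcome of this surgical phase is the occult metastatic rate of contralateral nodes (positive SNB"). The one forecast for this outcome follows in the same section: "with an expected SNB positive rate of excised nodes ranging from 25% to 40" per cent.
- **Outcomes, Surgical phase.** The outcome is given again, and alone: "Occult metastatic rate of contralateral nodes (positive SNB").
- **Sample size, Surgical phase.** The paragraph starts from all those enrolled in the phase: "75 patients will be considered for SNB". It goes on to forecast how many will drain contralaterally: "20%–30% (15–23 patients) are expected to have sentinel nodes on the opposite side of the neck". The precision is attached to that forecast: "An exact 95% CI for this proportion is expected to have precision of ±11" per cent.
- **Statistical methods, Surgical phase.** The whole section is one sentence: "We will quantify the proportion of SNB patients with sentinel nodes on the opposite side of the neck with an exact 95% CI".

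The Outcomes section makes the rate of contralateral drainage the primary outcome of the *imaging* phase. Under Planned interventions and in Table 3, the nodes excised in the surgical phase are the contralateral nodes found on imaging. A node counts as metastatic if it holds viable individual tumour cells or more.

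**The concern.** Having a contralateral sentinel node means that tracer drained there. Having a positive SNB means that tumour was found in the excised node. The first decides who is biopsied, and the second is the result of the biopsy. The Abstract and the Outcomes section make the second primary. The sample-size and statistical sections give a precision and an analysis for the first only.

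An analyst who follows the article as written would therefore produce an exact interval for drainage, which the imaging phase has already estimated. The document would give no denominator and no expected precision for the outcome on which the phase is to be judged. A reader may also take ±11% as the precision of the primary outcome, since it is the only precision stated for the phase. The denominator matters because the sole forecast, 25–40%, is per excised node, while the sample size is counted in patients.

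**Working it through.** **Inputs, all from the protocol article**

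- Surgical-phase patients: 75 (Sample size, Surgical phase).
- Expected with contralateral sentinel nodes: 20–30%, or 15–23 patients (same place).
- Expected positivity: 25–40% of excised nodes (Abstract, Methods and analysis).
- Interval: exact 95% CI (Sample size and Statistical methods).

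**Assumption.** Nodes per patient are not given. The per-node rate is therefore taken to apply per biopsied patient, which is exact if one node is excised from each.

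**Formula.** Clopper-Pearson for x events in n: lower limit = Beta(0.025; x, n−x+1), upper limit = Beta(0.975; x+1, n−x), where Beta(q; a, b) is the q-quantile. Half-width = (upper − lower)/2.

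**Step 1: reproduce the plan's ±11%**

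| Drainage | Estimate | Exact 95% CI | Half-width |
|---|---|---|---|
| 15/75 | 20.0% | 11.65–30.83% | 9.6 points |
| 23/75 | 30.7% | 20.53–42.38% | 10.9 points |

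The stated figure is the half-width at the upper end of the drainage range, so it is correct for the proportion it names.

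**Step 2: expected positives**

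- 15 × 0.25 = 3.75, rounded to 4; 15 × 0.40 = 6.
- 23 × 0.25 = 5.75, rounded to 6; 23 × 0.40 = 9.2, rounded to 9.

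**Step 3: precision for positive SNB among those biopsied**

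| Positive/biopsied | Estimate | Exact 95% CI | Half-width |
|---|---|---|---|
| 4/15 | 26.7% | 7.8–55.1% | 23.7 points |
| 6/15 | 40.0% | 16.3–67.7% | 25.7 points |
| 6/23 | 26.1% | 10.2–48.4% | 19.1 points |
| 9/23 | 39.1% | 19.7–61.5% | 20.9 points |

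**Step 4: precision for positive SNB over all 75**

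| Positive/all | Estimate | Exact 95% CI | Half-width |
|---|---|---|---|
| 4/75 | 5.3% | 1.5–13.1% | 5.8 points |
| 6/75 | 8.0% | 3.0–16.6% | 6.8 points |
| 9/75 | 12.0% | 5.6–21.6% | 8.0 points |

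**Step 5: sensitivity to the assumption.** Suppose each biopsied patient had two nodes with independent results. The chance of at least one positive would be 1 − 0.75² = 43.75% to 1 − 0.60² = 64%. Expected positives become 15 × 0.4375 ≈ 7 and 15 × 0.64 ≈ 10 of 15, and 23 × 0.4375 ≈ 10 and 23 × 0.64 ≈ 15 of 23. The exact half-widths are then 20.4–26.1 points among those biopsied and 7.2–9.6 points over all 75 (7/75 to 15/75). The precision among biopsied patients hardly moves, but the rate itself moves a good deal.

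**The case against.** **The stated precision is not wrong.** The article attaches ±11% to the drainage proportion, and it reproduces. It never claims that figure for SNB positivity. Over all 75 patients the precision for positive SNB is better than ±11%, and it is worse only among those biopsied. All of this stands. The fault is that the figure belongs to a different quantity from the primary outcome.

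**A separate analysis plan may hold the SNB analysis.** The Data sharing statement mentions one, and an article may leave detail to it. That would answer a complaint that a method is missing. It does not answer the contradiction here, because the article does state a precision and an analysis for this phase and both target something other than the named outcome.

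**Drainage is worth estimating again.** The phase objective is feasibility, the sample size is called pragmatic, and the injection and imaging route may differ from the imaging phase. This is fair, and it supports keeping drainage as a secondary estimate.

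**The forecast is in the outcome's own unit.** The outcome speaks of nodes, and so does the 25–40%. This is also fair, so node-level positivity should still be reported. But several nodes from one patient are not independent, and the sample size is in patients, so the denominator has to be named.

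Three stronger readings are tempting, and the documents do not support them.

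- *That the planned proportion is 100% by construction*, because only patients with contralateral nodes are biopsied. This holds only if the analysis sentence means patients actually biopsied. Read with the sample-size paragraph, it more naturally means the 75 considered for SNB.
- *That readers would set 25–40% against the background threshold* (prophylactic treatment "generally recommended when the estimated risk of occult nodal metastasis is >20" per cent) *and conclude in favour of treatment.* The article makes no such comparison. Under Planned interventions it says that the trial is not powered to change treatment on the SNB result.
- *That the plan's figures place the per-patient rate below 20%*, since 0.20 × 0.25 = 5% and 0.30 × 0.40 = 12%. This takes per-node positivity as per-patient positivity and counts unsampled necks as negative. With three independent nodes per patient the upper figure would be 0.30 × (1 − 0.60³) = 23.5%. A lower bound cannot show that a risk is low.

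**Conclusion.** The point holds as an internal contradiction. The Abstract and Outcomes section make positive SNB the surgical-phase primary outcome, while the sample-size precision and the only stated analysis address contralateral drainage, already the imaging-phase primary outcome.

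The ±11% is right for drainage in 75 patients and does not carry over. For positive SNB the expected half-width is about 19–26 points among the 15–23 biopsied, roughly twice the stated figure, and about 6–8 points over all 75. These sizes rest on the plan's own drainage and positivity ranges and on the per-node rate holding per patient.

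The finding does not extend to how the 20% treatment threshold should be applied, or to which side of it the result will fall.

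**What to change.** In the surgical-phase paragraphs under Sample size and Statistical methods:

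1. Make the primary analysis the proportion of patients with at least one positive contralateral SNB. Give an exact 95% CI over (a) all surgical-phase patients mapped and (b) those biopsied.
2. State the expected precision of each, about ±6–8 points for (a) and ±19–26 points for (b), with the assumption on nodes per patient. Label the existing ±11% as drainage only.
3. Keep the drainage proportion as a secondary estimate, with its denominator written out in place of the ambiguous term for SNB patients.
4. Report node-level positivity alongside, with excised nodes named as its denominator, and say that 25–40% is not a per-patient rate.
5. Note that (a) counts only sampled necks. Necks with no mapped contralateral node are not biopsied, so (a) is a lower bound on the occult metastatic rate.

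**Cost.** No extra patients, procedures or data items are evident: the change is to text. The stated precision among biopsied patients will look less favourable. Because recruitment is under way and the unit and denominator of a primary outcome are being fixed, the trial management group should decide whether a substantial amendment is needed, and the change should be made before surgical-phase results are seen.
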